### 10. SAFETY

#### 10.1 Decolonization Set

During the study, all serious adverse events (SAEs) are collected, fully investigated and documented in source documents and case report forms (CRF). Study duration encompasses the time from when the participant signs the informed consent until the last protocol-specific procedure has been completed, including a safety follow-up period. This is 42±14 days, or 1 year in case of an orthopaedic implant.

##### 10.1.1 Treatment by specialists

All surgeries will be performed in the supervision and participation of an advanced and experienced surgeon. The decolonization is ordered and supervised by the study investigators with professional experience in the prevention of orthopedic SSIs. The current medications of the operated study patients, as well as possible interactions, will be controlled by the Head of Pharmacy at the Balgrist.

##### 10.1.2 Definition and assessment of (serious) adverse events and other safety related events

###### *Adverse event*

An **Adverse Event (AE)** is any untoward medical occurrence in a patient or a clinical investigation participant administered the investigational product and which does not necessarily have a causal relationship with the investigational product. An AE can therefore be any unfavourable and unintended sign (including an abnormal laboratory finding), symptom, or disease temporally associated with the use of the investigational product, whether or not related to the investigational product.

###### *Assessment of Causality*

The investigators will make a causality assessment of the event in relation to the investigational product, based on the criteria listed in the ICH E2A guidelines:

| Relationship                                                                            | Description                                                                                                               |
|-----------------------------------------------------------------------------------------|---------------------------------------------------------------------------------------------------------------------------|
| Definitely                                                                              | Temporal relationship
Improvement after dechallenge*
Recurrence after rechallenge
(or other proof of drug cause) |
| Probably                                                                                | Temporal relationship
Improvement after dechallenge
No other cause evident                                          |
| Possibly                                                                                | Temporal relationship
Other cause possible                                                                             |
| Unlikely                                                                                | Any assessable reaction that does not fulfil the above conditions                                                         |
| Not related                                                                             | Causal relationship can be ruled out                                                                                      |
| *Improvement after dechallenge only taken into consideration, if applicable to reaction |                                                                                                                           |

#### *Adverse device effect (ADE, device or investigational product related)*

An ADE is any AE for which the causality assessment of the event in relation to the investigational product is possible, probable or definite.

A **Serious Adverse Event (SAE)** is classified as any untoward medical occurrence that:

- results in death,
- is life-threatening,
- requires in-patient hospitalization or prolongation of existing hospitalisation,
- results in persistent or significant disability/incapacity, or
- is a congenital anomaly/birth defect.

In addition, important medical events that may not be immediately life-threatening or result in death, or require hospitalisation, but may jeopardise the patient or may require intervention to prevent one of the other outcomes listed above should also usually be considered serious.

Examples of such events are intensive treatment in an emergency room or at home for allergic bronchospasm, blood dyscrasias or convulsions that do not result in hospitalization, or development of drug dependency or abuse.

SAEs will be followed until resolution or stabilisation. Participants with ongoing SAEs at study termination (including safety visit) will be further followed up until recovery or until stabilisation of the disease after termination.

So far, no serious adverse events as well as adverse events in relation to octenisan® md nasal gel and octenisan® washlotion have been observed in clinical studies.

#### *Unexpected Serious Adverse Drug Reaction*

An “unexpected” adverse drug reaction is an adverse reaction, the nature or severity of which is not consistent with the applicable product information (e.g. Investigator’s Brochure for drugs that are not yet approved and Product Information for approved drugs, respectively).

#### *Suspected Unexpected Serious Adverse Reactions (SUSARs)*

The Sponsor-Investigator evaluates any SAE that has been reported regarding seriousness, causality and expectedness. If the event is related to the investigational product and is both serious and unexpected, it is classified as a SUSAR.

#### *Assessment of Severity*

This study uses a severity grading scale as described in the “Common Terminology Criteria for Adverse Events CTCAE Version 4.

### **10.1.3 Reporting of serious adverse events (SAE) and other safety related events**

#### *Reporting of SAEs*

All SAEs must be reported immediately and within a maximum of 24 hours to the Sponsor-Investigator of the study. The Sponsor-Investigator will re-evaluate the SAE and return the form to the site.

SAEs resulting in death are reported to the local Ethics Committee (via local Investigator) within 7 days.

Equally, the donor schülke will be informed in the event of any of the below in section 10.1.3. The information to schülke will be entirely anonymous.

#### *Reporting of SUSARs*

A SUSAR needs to be reported to the local Ethics Committee (local event via local Investigator) within 7 days, if the event is fatal, or within 15 days (all other events).

#### *Reporting of Safety Signals*

All suspected new risks and relevant new aspects of known adverse reactions that require safety-related measures, i.e. so-called safety signals, will be reported to the Sponsor-Investigator within 24 hours. The Sponsor-Investigator will report the safety signals within 7 days to the local Ethics Committee (local event via local Investigator).

#### *Reporting and Handling of Pregnancies*

This study, all antibiotics and therapeutic surgeries, have no specific relation to pregnant or breast-feeding women and their children. However, for purely formality reasons, we will exclude pregnant and/or breastfeeding women..

Any pregnancy during the treatment phase of the study and within 30 days after discontinuation of study medication will be reported to the Sponsor-Investigator within 24 hours. The course and outcome of the pregnancy will be followed up carefully, and any abnormal outcome regarding the mother or the child should be documented and reported.

#### *Periodic reporting of safety*

An annual safety report on the participant is submitted once a year to the local Ethics Committee via the Lead Investigator. We, moreover, will perform statistical interim (futility) analysis on an annual basis.

#### **10.1.4 Follow up of (Serious) Adverse Events**

Participants terminating the study (either regularly or prematurely) with reported ongoing SAE, or any ongoing AEs of laboratory values or of vital signs being beyond the alert limit will return for a follow-up investigation. This visit will take place up to 30 days after terminating the treatment period. Follow-up information on the outcome will be recorded on the respective AE page in the CRF/eCRF. All other information has to be documented in the source documents. Source data have to be available upon request.

In case of participants are lost to follow-up, efforts will be made and documented to contact the participant to encourage him/her to continue study participation as scheduled. In case of minor AE, a telephone call to the participants is acceptable.

All new SAE or pregnancies that the investigators will be notified of within 30 days after discontinuation of investigational product will be reported in appropriate report forms and in the CRF/eCRF if required.

Follow-up investigations may also be necessary according to the investigator's medical judgment even if the participant has no AE at the end of the study. However, information related to these investigations does not have to be documented in the CRF/eCRF, but must be noted in the source documents.

## **11. STATISTICAL METHODS**

### **11.1 Main hypotheses**

Among our selected study participants with an elevated risk for SSI and wound revisions, the pre-surgical decolonisation may reduce surgical revisions by 5% (from 10% without decolonization to 5 % with decolonization) as compared to the untreated patient group.

### **11.2 Determination of Sample Size**

In our hospital, postoperative wound problems occur in at least 5% percent of all interventions. Incidence for both, revision surgery and/or SSI, in our selected patient population is set for 10% according to our clinical experience among the selected patient population that composes our study population.

We perform a superiority RCT with a power of 80% in favor of the decolonization. With 95% event-free surgeries in the decolonization arm versus 90% in the standard arm, we formally need 2 x 474 orthopedic surgery episodes, which we sum up to 2 x 500 surgeries (n = 1'000). A patient can be included several times as long as he/she gets not infected and has not witnessed postoperative wound problems.

### 11.3 Planned Analyses

All analyses will be performed for the entire study population. In a second step, all analyses will be separately performed according to subgroups of patients, based on the type of orthopaedic surgical procedure (e.g. arthroplasties, implant-related surgeries, etc.). We will use descriptive statistics and will perform group comparisons (using the Pearson- $\chi^2$ -test, the Fischer-exact-test, or the Wilcoxon-ranksum-test), as appropriate. We will also perform composite (SSI and wound problems) and separate (SSI or wound problems) multivariate analysis using a Cox regression model targeting the co-primary outcome variables. For the primary outcome parameter, univariable and multivariable results will be computed using a Cox regression analysis. Variables with a  $p$  value  $\leq 0.2$  in univariate analysis will be included in a stepwise forward selection process for multivariate analysis. Key variables will be checked for co-linearity and interaction. The number of variables in the final model is limited to the ratio of 1 variable to 5 to 8 outcome events. The significance level is  $p \leq 0.05$  (two-tailed).

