| Statistical analyses                                                  | Group comparisons by Pearson-Chi  -test or the Wilcoxon-ranksum-tests. Multivariate adjustments by Cox regression without cluster analysis. Stratifications according to the type of surgery. We will perform Intention-to-Treat and Per-Protocol analyses.                                                                                                                                                                                                                                                                                                                                                                                                                                                                                                                                                                                                                                                                                                                                                                                                                                                                |                            |                            |          |          |             |          |          |          |                              |              |                            |                            |                     |       |       |   |               |       |       |       |                          |        |        |        |                      |       |       |       |                  |       |     |       |                           |               |               |               |

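### Section 11.3 repeats every analysis inside an open list of surgery-type subgroups at an unadjusted 0.05, with no treatment-by-surgery-type interaction test, so subgroup conclusions would be unreliable

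*Protocol*

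**What the plan says.** Protocol section 11.3 sets two steps. First: "All analyses will be performed for the entire study population". Then: "In a second step, all analyses will be separately performed according to subgroups of patients, based on the type of orthopaedic surgical procedure". The subgroups are given only by example: "e.g. arthroplasties, implant-related surgeries, etc". The same paragraph gives one criterion for everything in it: "The significance level is $p \leq 0.05$ (two-tailed". It also says, while describing how the multivariable model is built: "Key variables will be checked for co-linearity and interaction".

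The synopsis row on statistical analyses adds only: "Stratifications according to the type of surgery".

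Section 11.2 sizes the trial for the whole population: "We perform a superiority RCT with a power of 80% in favor of the decolonization", and "With 95% event-free surgeries in the decolonization arm versus 90% in the standard arm". It arrives at 474 episodes per arm, rounded up to 500.

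**The concern.** The second step covers all analyses, so it includes the primary comparison. It is set up as separate tests within each subgroup, at the same level as the main test and without a stated status. Two errors become likely.

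- **False positives.** With no true effect, each added subgroup is another chance of a p-value at or below 0.05. A neutral trial could then be reported as showing benefit in one kind of surgery.
- **False contrasts.** With the same true effect in every kind of surgery, subgroups much smaller than the trial will often split into significant and non-significant ones. That invites the reading that decolonization works in some procedures and not in others. Separate p-values cannot support that reading; only a direct comparison of effects can.

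The open list makes the number of tests unknowable in advance. The overlap matters too. Section 3.2.1 counts almost any implant as an implant, so an arthroplasty that leaves a prosthesis in place belongs to both named groups. The same patients would be tested twice, and a single interaction factor could not be built from these groups as they stand.

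**Working it through.** **Inputs from the protocol.** Two-sided 0.05 (11.3); 10% versus 5% events, 80% power, 474 rounded to 500 per arm (11.2); 1:1 allocation (6.2.1).

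**Assumed, because the protocol does not say.** The number k of subgroups (2 to 6), equal sizes of 500/k per arm unless stated otherwise, and one test per subgroup.

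**1. The plan's own figure.** With p1 = 0.10, p2 = 0.05, mean 0.075 and difference 0.05:

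n = [1.96·√(2·0.075·0.925) + 0.842·√(0.10·0.90 + 0.05·0.95)]² / 0.05² ≈ 434.4, that is 435 per arm.

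With continuity correction: (434.4/4)·[1 + √(1 + 4/(434.4·0.05))]² ≈ 473.6, that is 474. The stated figure reproduces, and it rests on the whole-population test only.

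**2. No true effect, disjoint subgroups.** The chance of at least one p ≤ 0.05 is 1 − 0.95^k. The simulation columns use Pearson tests at a 10% event rate in both arms (400,000 trials).

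| k | 1 − 0.95^k | Simulated | Simulated, with overall test non-significant |
|---|---|---|---|
| 2 | 9.8% | 9.6% | 6.4% |
| 3 | 14.3% | 14.6% | 11.4% |
| 4 | 18.5% | 18.6% | 15.4% |
| 6 | 26.5% | 26.2% | 23.0% |

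**3. Overlap.** Suppose 200 arthroplasties per arm lie inside 350 implant surgeries per arm. Testing both groups gives 7.9%. Adding a non-implant group of 150 per arm gives 12.5%.

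**4. Fisher's exact test**, which 11.3 also allows. Exact calculation for four subgroups of 125 per arm gives 8.4% at a 5% event rate and 11.2% at a 10% event rate. For two subgroups of 250 per arm it gives 6.2% and 7.0%.

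**5. Uniform true effect of 10% versus 5%.** Power per subgroup with m per arm is

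Φ{[0.05·√m − 1.96·√(2·0.075·0.925)] / √(0.10·0.90 + 0.05·0.95)}.

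With power w, the chance that some subgroups are significant and others are not is 1 − w^k − (1 − w)^k.

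| k | m per arm | Power w | Mixed pattern |
|---|---|---|---|
| 1 (whole trial) | 500 | 85% | – |
| 2 | 250 | 56% | 49% |
| 3 | 167 | 41% | 73% |
| 4 | 125 | 32% | 78% |

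For k = 4: 1 − 0.322⁴ − 0.678⁴ = 0.78.

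These figures count one test per subgroup. Sections 11.3 and 11.3.2 also ask for composite and separate outcomes, univariable and multivariable models, and two analysis populations. The true number of (correlated) tests is therefore larger.

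**The case against.** The strongest reply is that subgroup lists, definitions and multiplicity rules usually belong in a statistical analysis plan, which is not at hand. That holds for the bare absence of a list or an alpha split. It does not cover what section 11.3 itself fixes: separate tests as the method, all analyses as the scope, and 0.05 as the only threshold. A later plan would have to overrule that text, not merely complete it.

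A second reply is that the interaction check already deals with this. That check belongs to the building of the multivariable model. It does not name treatment by surgery type and does not govern the subgroup step. Equally, the protocol gives no rule for comparing subgroups, so the false contrast is a likely misreading and not a planned inference.

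A third reply is that looking at implant surgery separately has a design reason, because its outcome window is one year instead of six weeks. That is fair. It justifies showing the estimate, not testing it alone at 0.05.

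A reader might go further and infer any of the following, none of which the document supports:

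- **The trial's main error rate is inflated.** It is not. The whole population is analysed first, the hypothesis in 11.1 and the sample size in 11.2 concern it alone, and its 5% error is untouched.
- **There is no order among the analyses.** There is one: whole population, then subgroups.
- **One fixed false-positive rate, such as 15% to 19%, follows from the plan.** Those values belong to four disjoint subgroups under Pearson tests, and the number is nowhere stated.
- **A mixed pattern is to be expected whatever the number of subgroups.** With two equal subgroups it is about an even chance.
- **The sponsor intends efficacy claims by surgery type.** No section says so.

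**Conclusion.** The point holds as a minor one. Section 11.3 commits to separate tests of every analysis in an open and partly overlapping set of surgery-type subgroups at an unadjusted 0.05. It provides no direct test of whether the effect differs by surgery type.

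With no effect, the chance of at least one significant subgroup runs from about 10% (two disjoint subgroups) to 26% (six). It is about 8% for the two named examples at the assumed sizes, and as low as about 6% for two disjoint subgroups under Fisher's test. With a uniform 10% versus 5% effect and two to four equal subgroups, conflicting results arise in about half to three quarters of trials.

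All of this depends on the assumed number, size and overlap of the subgroups and on the test used. Every case examined lies above 5%, but no single figure can be attributed to the protocol. The harm is limited to secondary conclusions about surgery types.

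**What to change.** Replace the subgroup sentence in 11.3 with text to this effect:

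> The effect of decolonization by surgery type is exploratory. It is assessed by one treatment-by-surgery-type interaction test in the full ITT population, using mutually exclusive classes. Subgroup estimates are shown with 95% confidence intervals. No claim of efficacy rests on a within-subgroup p-value.

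The sponsor should choose and name the classes; arthroplasty, other implant surgery and surgery without implant would be one workable set. The statistical row of the synopsis should be brought into line.

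**Cost.** A change of wording and one model term; sample size, visits and the primary significance level stay as they are. Procedure type must be recorded, because the variable lists in the synopsis and the study schedule name only the indication for surgery and the presence of osteosynthesis. The interaction test will have low power, and no confirmatory claim for a single surgery type will be possible. The current design could not support such a claim reliably in any case.

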## 5. STUDY OUTCOMES

### Primary outcomes:

- Remission (and inversely superficial or deep-space SSI and revision surgeries for non-infected wound problems; composite primary outcome) at 6 weeks (and/or a 1 year for surgeries with implant)

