### 9. STUDY ASSESSMENTS

#### 9.1 Assessment of primary outcome

Judged by local wound healing (healed vs delayed wound healing according to Reference). The wound healing will be assessed visually by orthopaedic surgeons. Wound nurses and the study investigators may help in the assessment of wound problems, but in case of doubtful cases, the opinion of the treating physician will dominate the decision upon the presence or absence of wound problems and/or infection.

Persistent postsurgical pain, serum laboratory markers, or the patient's subjective wound feelings will not serve as objective criteria for wound healing (or in the contrary, wound discharge and dehiscence). A wound problem solely due to stitches and localized suture problems will not count as a wound problem. A keloid or altered pigment features will not be counted as a problem in this trial. Remission is defined as the absence of any problems and as the absence of any clinical signs of infection.

The primary outcome will be assessed on both, the Intention-to-treat and the per-protocol populations.

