#### 11.3.1 Interim analysis and early termination

We will perform one interim analysis one year (+/- 2 months) after the inclusion of the first patient. If group comparison between the decolonization and non-decolonization arms are striking and statistically significant in terms of any study objectives, the independent Data Monitoring committee will decide upon the interruption and early termination of the trial. Otherwise, the study continues. Of note, the Data Monitoring committee has the right to call on a premature, additional interim analysis.

If the crude group comparison analysis is not sufficiently meaningful, we will perform a futility analysis to check if the expected statistical power for the final analysis will not be  $< 30\%$  and therefore unacceptable. If it is lower than  $30\%$ , we will consider the trial will not be able to demonstrate the result, and the recruitment will be no more ethical. The most frequent conditional power evaluated under the current trend (i.e. using the information from the collected data) will be assessed. It was demonstrated that futility analyses decrease the statistical power of the final analysis in superiority trials, but in our knowledge, this topic was not explored for non-inferiority trials. To balance (at least partially) this loss of power, we may recruit 100 supplementary patients per arm. E.g. approximately 600 episodes in each randomization arm.

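### Section 11.3 calls the composite and its separate parts co-primary at one unadjusted 5% level, while the synopsis, section 5 and the sample size rest on a single composite primary outcome

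*Protocol*

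**What the plan says.** - **Synopsis and section 5** name one primary outcome, given as remission or its inverse: "superficial or deep-space SSI and revision surgeries for non-infected wound problems; composite primary outcome".
- **Section 11.2** sizes the trial for one pair of event rates, 90% against 95% event-free surgeries: "We perform a superiority RCT with a power of 80% in favor of the decolonization". It reports 474 episodes per arm, raised to 500.
- **Section 11.3** plans "composite (SSI and wound problems) and separate (SSI or wound problems) multivariate analysis using a Cox regression model targeting the co-primary outcome variables". Its next sentence returns to the singular: "For the primary outcome parameter, univariable and multivariable results will be computed using a Cox regression analysis". The only significance level is p ≤ 0.05, two-tailed. There is no division of alpha, no testing order, and no rule on whether one or all of the co-primary outcomes must be significant.
- **Section 11.3.1** refers the trial to the data monitoring committee at the interim if the arms differ in a way that is striking and "statistically significant in terms of any study objectives".

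**The concern.** A statistical analysis plan can add detail to a primary outcome, but it should not have to choose between two versions of it. Here the outcome sections and the sample size point to one composite, while the analysis section points to two or three co-primary variables, depending on how its sentence is read. The meaning of a co-primary set depends on its success rule. If any one success is enough, the type I error exceeds the nominal level unless alpha is shared. If all must succeed, type I error falls but power has to be calculated for the joint event. The protocol states neither rule, and its sample size fits neither.

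The trial is unblinded (6.2.2), and the treating physician's opinion decides doubtful wound or infection cases (9.1). It is therefore worth leaving no choice among composite, SSI and wound problems open until the data are seen.

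**Working it through.** **Inputs from the protocol.** Event rates 10% and 5%, power 80%, 474 raised to 500 per arm (11.2); two-sided 0.05 (11.3); 1:1 allocation (6.2.1).

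**Step 1: reproduce the sample size.** With p̄ = 0.075 and d = 0.05:

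n = [1.960·√(2·0.075·0.925) + 0.8416·√(0.10·0.90 + 0.05·0.95)]² / 0.05² = (0.7301 + 0.3121)² / 0.0025 ≈ 434.4, or 435 per arm.

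With the continuity correction:

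n′ = (n/4)·[1 + √(1 + 4/(n·d))]² = 108.6 × (1 + √1.1841)² ≈ 473.6, or 474 per arm.

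This matches the protocol exactly. One-sided variants give 343, or 382 with the correction, and do not match. The calculation is thus for one outcome at the full two-sided 0.05, with nothing set aside for further primary outcomes. At 500 per arm the power is 85%, or 82% with the correction.

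**Step 2: error if any one outcome suffices.** The protocol does not give the split or overlap of SSI and wound problems, so these are assumed. The composite rate is 5 to 10%, SSI is 20 to 70% of the events that fall in only one category, and 0 to 30% of events count as both. Under no true effect, with 500 per arm, unadjusted two-sided chi-square tests and 500,000 simulated trials per scenario:

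| Quantity | Range over scenarios |
|---|---|
| Composite alone significant | 4.8 to 5.0% |
| At least one of composite, SSI, wound problems | 10.1 to 11.5% |
| The same, counting only results in favour of decolonization | 5.0 to 5.8% (nominal 2.5%) |
| At least one of the two parts only | 8.9 to 9.8% |
| All three significant | 0.1 to 0.8% |

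The simulated rates lie below the value for three independent tests, 1 − 0.95³ = 14.3%, and below the Bonferroni bound of 15%, because the composite contains its parts.

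**Step 3: power if all must succeed.** Assume that both parts are halved, that there is no overlap, and that the parts are independent, at 500 per arm without continuity correction:

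| SSI share of the 10% | Power, SSI | Power, wound problems | Product |
|---|---|---|---|
| 20% (2% vs 1%; 8% vs 4%) | 0.255 | 0.760 | 0.19 |
| 30% (3% vs 1.5%; 7% vs 3.5%) | 0.359 | 0.699 | 0.25 |
| 50% (5% vs 2.5% each) | 0.548 | 0.548 | 0.30 |

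None of these is near 80%.

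**Step 4: cost of keeping three primaries with any one sufficient.** Bonferroni at 0.05/3 = 0.0167 needs 620 per arm for the composite at 10% against 5% with continuity correction (580 without). At 500 per arm, power on the composite would be 69% with the correction or 73% without. Section 11.3.1 considers at most about 600 per arm.

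**The case against.** The strongest reply is that co-primary is only a loose label. The sentence is introduced as something done in addition, the next one speaks of a single primary outcome parameter, and the hypothesis and sample size each use one pair of rates. In its strict sense, co-primary means that all outcomes must succeed, and then type I error is not inflated. The loose-label reading is quite possible, but it means that the word is wrong and should be changed. The strict reading avoids inflation only by giving up the stated power (step 3).

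Three stronger readings are tempting, and the documents do not support them:

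- *The 5% level is not held.* The protocol states a significance level and promises no error rate across a family of outcomes. For the composite alone, 5% holds, leaving the interim look aside.
- *Success may be claimed on SSI or wound problems alone.* No final-analysis rule says so. The phrase "statistically significant in terms of any study objectives" concerns referral to the committee at the interim and is not a final success criterion.
- *The per-protocol and subgroup analyses are further primary tests that add to the error.* Section 9.1 does say "The primary outcome will be assessed on both, the Intention-to-treat and the per-protocol populations", and 11.3 says "all analyses will be separately performed according to subgroups of patients". But 11.3.2 presents the per-protocol analyses as a repeat, and 11.3 places the subgroups in a second step. The protocol gives neither the number of subgroups nor the size of the per-protocol set, so no figure can be put on them. How such analyses are ranked or modelled is commonly left to a statistical analysis plan.

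Two limits on the calculation stand: the SSI and wound-problem split is assumed, and chi-square tests replace the planned Cox models.

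**Conclusion.** The contradiction is in the protocol's own text and should be corrected. One composite is named and powered; 11.3 then calls the composite and separate outcomes co-primary at a single unadjusted level with no success rule. The two-sided chance of at least one false positive would be about 10 to 11.5% if any of the three sufficed, with about 5 to 6% in favour of decolonization against 2.5%. It would be about 9 to 10% if only the two parts are meant. Requiring all to succeed would leave joint power for the two parts at about 19 to 30%.

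The error range changes little across the assumed splits and overlaps. The power range depends more on the split, and also on halving both parts and treating them as independent. The composite test itself is sound at 5%, so this is a defect in the decision rule as written and not in the sample size.

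**What to change.** In 11.3, replace the reference to co-primary outcome variables with the single composite of the synopsis and section 5 as sole primary outcome. Test it once at two-sided 0.05, in the ITT population as defined in 11.3.2, by the two-proportion comparison used for the sample size. Label the separate SSI and wound-problem analyses, and the univariable and multivariable Cox models, as secondary or supportive.

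The 474 per arm, raised to 500, then stands unchanged. The cost is a wording amendment and giving up a claim of success on one component alone. If the sponsor wants to keep that claim, the protocol has to state an alpha rule and derive the sample size again; under Bonferroni across three outcomes this is about 620 per arm.
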